### 16.2 Five-point scoring system for small intestinal mucosal injury

**Table 7 Five-point scoring system to assess intestinal mucosal injury**

| Category                                                                                             | Score |
|------------------------------------------------------------------------------------------------------|-------|
| Normal                                                                                               | 0     |
| Petechiae/red spot (demarcated, usually circular, area of crimson mucosa with preservation of villi) | 1     |
| Small number of erosions (1–4 erosions)                                                              | 2     |
| High number of erosion (>4 erosions)                                                                 | 3     |
| Mucosal breaks (large erosion and/or ulcer)                                                          | 4     |

## 17. APPENDIX 3 – GASTROINTESTINAL SYMPTOM

### SCORE

Symptoms are categorized as four types: abdominal pain, bloating, acid reflux, and belching.

Each symptom includes a five-level scoring system (degree and frequency are scored separately; the maximum score = 4 + 4 = 8 points).

**Table 8 Five-point scoring system to assess gastrointestinal symptoms**

| Score | Symptom                                                                                   | Frequency                  |
|-------|-------------------------------------------------------------------------------------------|----------------------------|
| 0     | No symptom                                                                                |                            |
| 1     | Mild: mild symptoms, need to pay attention to feel                                        | once per week              |
| 2     | Moderate: self-conscious obvious symptoms, but does not affect work and life              | 2-3 times per week         |
| 3     | Severe: self-conscious obvious symptoms, affect work and life                             | 4-5 times per week         |
| 4     | Extremely severe: self-conscious very obvious symptoms, seriously affecting work and life | Almost daily or consistent |

## 18. APPENDIX 4 – TREATMENT PRINCIPLES OF GASTROINTESTINAL BLEEDING AND MUCOSAL INJURY

Regulation rules in Cardiology

DAPT should be discontinued immediately. After three days after stopping the bleeding by electronic gastroscopy:

- 3) If gastrointestinal injury is entirely controlled without reoccurrence of active bleeding, and hemoglobin is maintained at the level of  $\geq 9$  g/dL (90 g/L), clopidogrel monotherapy (75 mg, daily) should be firstly administered as soon as possible and aspirin (100 mg, daily) should be resumed at the 5th day after hemostasis. Times, types and doses of medications should be recorded in detail.
- 4) If active minor or occult bleeding still exists, or the level of hemoglobin fluctuates above 10 g/L in different days (monitor the blood routine test if necessary), only low molecular weight heparin (LMWH, hypo, daily) is used. Then at the 7th day after hemostasis, stop the LMWH and resume DAPT

(doses and frequencies as above).

## 18.1 Fecal Occult Blood (FOB) Tests

Precautions before testing:

- 1) Do not test during the period of menstrual bleeding, hemorrhoid bleeding or anal fissure;
- 2) To avoid affecting the judgment of FOB results, it is forbidden to take iron supplement, meat, liver, blood, and green vegetables within three days before the examination to avoid affecting the judgment of FOB results.

### Treatment of patients with positive results:

**Before randomization:** For patients with positive FOB result, the test should be repeated for 2 consecutive days, and the complete blood count should be performed at the same time. If the FOB test is continuously positive with a decrease in hemoglobin (a drop of more than 10g/L compared to baseline screening), AMCE should be performed to confirm the lesion (for free), and even if no clear lesions are found, it should be considered that occult small intestinal bleeding exists. The patient will be treated according to the principle of gastrointestinal bleeding treatment, and is ineligible for study enrollment. If the continuously positive FOB result continues without hemoglobin reduction, the blood routine test should be monitored at the same time as each fecal occult blood test. If the hemoglobin drops more than 10g/L (compared with the first blood routine test after positive FOB result), AMCE should be performed to confirm the lesion (for free). Then the patient will be treated according to the principle of gastrointestinal bleeding treatment and is ineligible for study enrollment. If FOB test turns negative in a repeated test, no treatment will be given.

**After randomization:** For patients with positive FOB result, the test should be repeated for 2 consecutive days, and the complete blood count should be performed at the same time. If the FOB test is continuously positive with a decrease in hemoglobin (a drop of more than 10g/L compared to baseline screening), AMCE should be performed to confirm the lesion (for free), and even if no clear lesions are found, it should be considered that occult small intestinal bleeding exists. Breaking the blinding shall be performed immediately, and the patient will be treated according to the principle of gastrointestinal bleeding treatment. If the continuously positive FOB result continues without hemoglobin reduction, the blood routine test should be monitored at the same time as each fecal occult blood test. If the hemoglobin drops more than 10g/L (compared with the first blood routine test after positive FOB result), AMCE should be performed to confirm the lesion (for free), and even if no clear lesions are found, it should be considered that occult small intestinal bleeding exists.

Breaking the blinding shall be performed immediately, and the patient will be treated according to the principle of gastrointestinal bleeding treatment. The identification of time of the gastrointestinal bleeding event is the date of the first positive FOB result. If FOB test turns negative in a repeated test, no treatment will be given.

## **18.2 The treatment procedure of clinically-driven or AMCE-positive gastrointestinal (GI) bleeding**

- 1) The patient with GI bleeding before randomization will be treated in accordance with the following (Appendix 1-3) rules. The patient will be no longer randomized and the study is terminated.
- 2) The patient with GI bleeding after randomization should be confirmed by gastroscopy, and endoscopic treatment is taken if necessary. If the lesion is not clear, the AMCE examination is performed to observe the small intestine lesions. If no clear bleeding is found, colonic bleeding is suspected, and further colonoscopy should be performed.
- 3) After obtaining the consent of principal of the participating research site, the treating physician could unblind for this patient (Part 5.4), conduct hemostatic treatment and adjust antiplatelet therapy according to the following rules (Appendix 1-3). Antiplatelet therapy could be at physician's discretion according to local standard care after curing the bleeding.
- 4) This patient will not terminate study, but only clinical 12-month follow-up (without AMCE examination) is needed.

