### **5.5.2 Methods for breaking the blinding in the study**

In the event of a medical emergency, in which knowledge of the investigational drug is critical to the subject's medical management, the blind for that subject may be broken by the treating physician. Before breaking the blinding, the consent of the research leader of the participating research site should be obtained and the relevant researchers and monitors should be informed. At the same time, the events leading to break the blinding and the blind code information should be recorded in detail. After breaking the blinding, the subject will not receive any study drug, and the treated physician can take corresponding bail-out measures according to local standard of care. The study drugs cannot be resumed even if the condition of subject is stable, while researchers still need to conduct clinical follow-up for 12 months for the subject with broken blinding, and AMCE examination is still required. Researchers should withdraw the study drugs from the patients whose blinding was broken.

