### **5.9.2 Permanent discontinuation from study medication due to reasons below:**

- Patient decision. The patient is at any time free to discontinue treatment, without prejudice to further treatment.
- Investigator's decision:
  - 1) Incorrectly enrolled patient in whom the inclusion/exclusion criteria violation would put the patient at undue risk.
  - 2) Investigators judge that due to adverse events related to any kind of study drug, continuous administration of this study drug would put the patient at undue risk.

Details on the date, duration and cause of each permanent discontinuation of study drugs should be fully recorded into the appropriate section of the EDC. When any of the study drugs are permanently discontinued, further antiplatelet therapy should be given to the subject according to attending physician's discretion. Any remaining study drugs should be returned to the local research site at the next scheduled follow-up visit. Although these subjects are no longer receiving any study drug, they should also be followed up until 12 months. Patients who permanently discontinue study drugs after randomization are still required to undergo AMCE examination, and investigators are required to withdraw study drugs from patients after discontinuation. Patients who permanently discontinue study drugs before randomization only needed to be followed up by telephone at 12 months.

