### **6.2.3 Face-to face follow-up procedure at 12 months (for randomized subjects)**

- Assess for adverse events may include, but not be limited to MI, stroke, revascularization, bleeding and ST
- Conduct the third AMCE examination to observe gastrointestinal mucosal lesions
- Review concomitant medications with subject
- Recycle and count all of remaining study drugs

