#### **3.4.2 Methods for unblinding patients' treatment assignment**

In emergency situations, in which knowledge of the investigational drug is critical to the subject's medical management, the blind for that subject may be broken by the treating physician to provide optimal management. Before breaking the blinding, the consent of the research leader of the participating research site should be obtained and the relevant researchers and monitors should be informed. At the same time, the events leading to break the blinding and the blind code information should be recorded in detail. After breaking the blinding, the subject will not receive any study drug, and the treated physician can take corresponding bail-out measures according to local standard of care. The study drugs cannot be resumed even if the condition of subject is stable, while researchers still need to conduct clinical follow-up for 12 months for the subject with broken blinding, and AMCE examination is still required. Researchers should withdraw the study drugs from the patients whose blinding was broken.

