## 4 Primary and secondary variables

### 4.1 Primary variable

The primary endpoint is the incidence of gastric or intestinal mucosal injury occurring within 12 months after enrollment, defined as erosion, ulceration or bleeding detected by either planned AMCE or clinically-driven endoscopy. Specifically, gastrointestinal erosion is defined as superficial mucosal breaks with a diameter of  $<5$  mm.

Gastrointestinal ulcer is defined as a mucosal break with a diameter  $\geq 5$  mm, typically covered with fibrin.

Situations below can be regarded as valid primary endpoint results, including:

- Successful completion of the AMCE examination at 6 months after randomization (i.e., 12 months after enrollment), regardless of the results of examination;
- Although the third AMCE examination at 6 months after randomization is not done, the second examination at 6 months after PCI reports new-onset gastric or small intestinal mucosal lesions;
- AMCE or gastroscopy examination driven by the occurrence of gastrointestinal bleeding at any time during the whole study period observes new-onset gastric or small intestinal mucosal lesions.

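### Protocol 18.2(4) waives the 12-month AMCE after a post-randomisation GI bleed, against 5.5.2, 5.9.2 and SAP 3.4.2 for bleeders who are unblinded or off drug, so a bleeder with no new lesion can drop out of the primary analysis

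*Supplement*

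**What the plan says.** Protocol v1.4 section 18.2 deals with GI bleeding after randomisation. Item 2 sends the patient to gastroscopy and, if the lesion is unclear, to AMCE. It then adds: "If no clear bleeding is found, colonic bleeding is suspected, and further colonoscopy should be performed". Under item 3, "the treating physician could unblind for this patient (Part 5.4), conduct hemostatic treatment and adjust antiplatelet therapy according to the following rules". Item 4 ends the sequence: "This patient will not terminate study, but only clinical 12-month follow-up (without AMCE examination) is needed".

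Other sections give the opposite instruction for patients who can be the same people:

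- Protocol 5.5.2, on breaking the blind, requires 12-month clinical follow-up "for the subject with broken blinding, and AMCE examination is still required". It also bars any return to study drug.
- SAP 3.4.2 repeats this: "researchers still need to conduct clinical follow-up for 12 months for the subject with broken blinding, and AMCE examination is still required".
- Protocol 5.9.2: "Patients who permanently discontinue study drugs after randomization are still required to undergo AMCE examination".
- Protocol 6.2.3 lists for the 12-month visit of randomised subjects, without exception: "Conduct the third AMCE examination to observe gastrointestinal mucosal lesions".

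SAP 6.1 analyses the primary endpoint in patients with a valid primary result. SAP 4.1 gives three routes to one:

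1. a completed 12-month AMCE, whatever it shows;
2. no 12-month AMCE, but a new lesion at the 6-month AMCE;
3. an AMCE or gastroscopy "driven by the occurrence of gastrointestinal bleeding at any time during the whole study period observes new-onset gastric or small intestinal mucosal lesions".

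**The concern.** A site with an unblinded bleeder cannot obey both 18.2(4) and 5.5.2, and nothing says which prevails. The cross-reference in 18.2(3) does not help: it points to Part 5.4, which covers incorrect enrolment, whereas emergency unblinding is in 5.5.2.

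The choice matters because routes 2 and 3 in SAP 4.1 accept positive findings only. Route 1 is the only way to record a valid negative, and it is the only route left to a bleeder in whom no new lesion has been seen. If 18.2(4) is followed, that patient has no primary outcome. Membership of the primary analysis population then turns on an event after randomisation that may be related to treatment, and on which paragraph the site reads.

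**Working it through.** **Which bleeders face a contradiction**

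| Bleeder after randomisation | Rule waiving AMCE | Rule requiring AMCE | Reading |
|---|---|---|---|
| Unblinded under 18.2(3) | 18.2(4) | 5.5.2, SAP 3.4.2 | Direct contradiction |
| Permanently off study drug | 18.2(4) | 5.9.2 | Direct contradiction |
| Neither | 18.2(4) | 6.2.3 schedule only | Specific exception to a general schedule |

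**Which bleeders lose their primary result if AMCE is waived (SAP 4.1)**

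| New lesion at 6-month AMCE | New lesion at bleed-driven examination | Valid result without 12-month AMCE? |
|---|---|---|
| Yes | Yes or no | Yes, route 2 |
| No | Yes | Yes, route 3 |
| No | No | No |

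Only the last row is affected. The patient whom 18.2(2) sends on to colonoscopy is an example, so the protocol foresees the case. Protocol 11.1 has no counterpart to route 2. Read alone, it would also lose a bleeder whose only new lesion was seen at 6 months.

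**Reproducing the planned design**

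Inputs from SAP 5: 47% on DAPT, 30% on monotherapy, 1:2 allocation, two-sided 0.05, 90% power, 20% loss. A two-proportion z test with pooled null variance needs 127 + 254 = 381 evaluable patients (stated: 384). Power at 128/256 is 90.3% (stated: 90%). 384/0.80 = 480 randomised, as stated.

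**Size of the effect under assumed loss rates**

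The documents give no rate of lesion-negative bleeding, so the shares below are assumptions, with bleeds taken as commoner on DAPT. Let b0 and b1 be the shares of evaluable patients lost on DAPT and monotherapy. The remaining numbers are 128(1−b0) and 256(1−b1). The observed rates depend on what the lost patients' 12-month AMCE would have shown:

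- all events: (0.47−b0)/(1−b0) against (0.30−b1)/(1−b1);
- their arm's average risk: 0.47 against 0.30;
- all non-events: 0.47/(1−b0) against 0.30/(1−b1).

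| Lost, DAPT/mono | Remaining n | All events | Arm-average | All non-events |
|---|---|---|---|---|
| None | 128/256 | – | 17.0 points, power 90.3% | – |
| 1%/0.5% | 126.7/254.7 | 16.8 points, 89.6% | 17.0, 90.1% | 17.3, 91.1% |
| 2%/1% | 125.4/253.4 | 16.6 points, 88.8% | 17.0, 89.9% | 17.7, 91.8% |
| 5%/2% | 121.6/250.9 | 15.6 points, 84.5% | 17.0, 89.2% | 18.9, 94.1% |

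For 2%/1% and all events: (0.47−0.02)/0.98 = 45.9%, (0.30−0.01)/0.99 = 29.3%, difference 16.6 points. In patients, 2%/1% is 128 × 0.02 ≈ 3 and 256 × 0.01 ≈ 3; 5%/2% is about 6 and 5.

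**What SAP 8 covers**

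At the planned 20% loss, 32 of 160 DAPT and 64 of 320 monotherapy patients have no outcome. Expected observed events are 0.47 × 128 = 60.2 and 0.30 × 256 = 76.8.

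- Best case: (60.2 + 32)/160 = 57.6% against 76.8/320 = 24.0%, a difference of +33.6 points.
- Worst case: 60.2/160 = 37.6% against (76.8 + 64)/320 = 44.0%, a difference of −6.4 points.

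These bounds contain any outcome assigned to the lost bleeders. They describe all missing outcomes together and are not an effect of 18.2(4).

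**The case against.** The waiver has a sensible rationale. The bleeder has just had gastroscopy and, if needed, AMCE. Where a new lesion was seen, the binary endpoint is settled and another capsule adds nothing. Losing a patient takes several conditions at once: a bleed after randomisation, no new lesion at the bleed, none at the 6-month AMCE, and a site that follows 18.2(4). The 6-month condition is a real restriction, because only ulceration or bleeding bars randomisation, so patients with new erosions can be randomised and keep a valid result through route 2. The 20% allowance absorbs the numbers, and SAP 8 prespecifies complete-case, best-case, worst-case and tipping-point analyses. All of this stands. It makes the point small but does not remove the contradiction.

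It could also be argued that the endpoint definition includes bleeding, so a lesion-negative bleed might count as an event. The validity rule for a bleed-driven examination names only new lesions, and a suspected colonic source lies outside a gastric or small-intestinal endpoint. The text does not settle it.

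A reader might infer three stronger claims that the documents do not support:

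- That 18.2(4) contradicts the other sections for every bleeder. It does so only for those unblinded or permanently off drug; 18.2(3) permits unblinding and does not require it.
- That the occult bleeders of 18.1, whose unblinding is mandatory, are lost as well. The heading of 18.2 leaves unclear whether they fall under it, so the point does not rest on them.
- That the rule biases the trial in a known direction. If bleeds are commoner on DAPT, the contrast shrinks when the lost patients are events and widens when they are not.

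**Conclusion.** The point holds and is minor. The current protocol and SAP give incompatible instructions on the 12-month AMCE for a bleeder who is unblinded or permanently off drug. A bleeder with no new lesion at 6 months or at the bleed leaves the mITT population if the waiver is followed. SAP 8 and 9.2 also speak of all randomised subjects or the FAS, but that does not help: the patient has no observed outcome there either, and no imputation is specified for the primary analysis. The best and worst cases bracket the missing outcome without returning the patient to the primary analysis.

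The number affected is unknown and probably a handful. Under the assumed 2%/1% loss the contrast moves by −0.4 to +0.7 points. The wider −1.4 to +1.9 needs 5%/2% loss with every lost patient given the same outcome, and nothing in the documents supports that rate.

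**What to change.** Amend 18.2(4) so that a randomised bleeder who does not already have a valid positive primary result still has the scheduled 12-month AMCE unless it is medically contraindicated, with the reason recorded. This agrees with 5.5.2, 5.9.2 and SAP 3.4.2 and keeps the waiver where it does no harm. In the SAP, add a count by arm of post-randomisation bleeders with no valid primary result. The endpoint definition stays as it is.

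The cost is one sentence in each document and a few AMCE visits that 6.2.3 already schedules. There are two limits. A late AMCE may look normal after PPI treatment and changes in antiplatelet therapy. The contraindication clause also leaves some missingness to a physician who may be unblinded, which is why the reason should be recorded and the count reported.

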## **18.3 The treatment principle of clinically-driven or AMCE-positive gastrointestinal (GI) bleeding**

### **Gastroenterology treatment rules:**

- 1) Patients with a definite diagnosis of GI bleeding should undergo endoscopic hemostasis as soon as possible with stable hemodynamics. The specific hemostasis methods can be implemented according to the experience of the endoscopy center of each hospital, such as hemostatic clips, APC, rinse with ice adrenal solution, heat probe, etc., plus PPI treatment. Medications: for gastric ulcer, PPI + gastric mucosal protective agent for 6 weeks, for duodenal ulcer, PPIs for 4 weeks. If patients with *Helicobacter pylori* (HP) infection requires eradication therapy, Quadruple therapy for 2 weeks could be performed.

2) Patients with GI bleeding and shock should be treated in accordance with routine treatment such as hemorrhagic shock monitoring, blood transfusion, fluid infusion, and hemostasis.

**Table 2 The specific procedures**

[figure not shown]

### Cardiology treatment rules:

DAPT should be discontinued immediately. After three days after stopping the bleeding by electronic gastroscopy:

1) If gastrointestinal injury is entirely controlled without reoccurrence of active bleeding, and hemoglobin is maintained at the level of  $\geq 9$  g/dL (90 g/L), clopidogrel monotherapy (75 mg, daily) should be firstly administered as soon as possible and aspirin (100 mg, daily) should be resumed at the 5th day after hemostasis. Times, types and doses of medications should be recorded in detail.

2) If active minor or occult bleeding still exists, or the level of hemoglobin fluctuates above 10 g/L in different days (monitor the blood routine test if necessary), only low molecular weight heparin (LMWH, hypo, daily) is used. Then at the 7th day after hemostasis, stop the LMWH and resume DAPT (doses and frequencies as above).

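### The Appendix 4 cardiology bleeding rules are written for patients on DAPT; followed literally, they would put an unblinded group B or C bleeder on two open-label antiplatelet drugs

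*Supplement*

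**What the plan says.** The cardiology rules appear twice in protocol v1.4, at the head of Appendix 4 and in 18.3. They begin: "DAPT should be discontinued immediately. After three days after stopping the bleeding by electronic gastroscopy". Two branches follow.

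- **Branch 1** (injury controlled, no renewed bleeding, hemoglobin at least 90 g/L): "clopidogrel monotherapy (75 mg, daily) should be firstly administered as soon as possible", and then "aspirin (100 mg, daily) should be resumed at the 5th day after hemostasis".
- **Branch 2** (minor or occult bleeding persists, or hemoglobin fluctuates): heparin alone, and on day 7 after hemostasis "stop the LMWH and resume DAPT (doses and frequencies as above".

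Two routes lead to these rules after randomization. Under 18.2, item 3, "the treating physician could unblind for this patient (Part 5.4), conduct hemostatic treatment and adjust antiplatelet therapy according to the following rules (Appendix 1-3". Under the post-randomization part of 18.1, for a persistently positive fecal occult blood (FOB) test with a hemoglobin drop, "Breaking the blinding shall be performed immediately, and the patient will be treated according to the principle of gastrointestinal bleeding treatment". Neither route depends on the randomized group.

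Other text leaves the choice of drug to the physician. The last sentence of 18.2, item 3, permits discretion "according to local standard care after curing the bleeding". Section 5.5.2, repeated in SAP 3.4.2, refers to local standard of care once the blind is broken, and says study drug is not restarted. Section 5.9.2 leaves therapy after permanent discontinuation to the attending physician.

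**The concern.** The rules fit a patient who bleeds before randomization, when everyone is on DAPT, and they fit group A. They do not fit group B (aspirin plus clopidogrel placebo) or group C (clopidogrel plus aspirin placebo). An unblinded patient from either group who bled on one active drug would, on the printed wording, be given two within days of hemostasis.

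That runs against the protocol's own reasoning. Section 5.3, criterion 3(b), lists bleeding as an example of why a patient cannot continue DAPT, and exclusion criterion 20 removes patients for whom monotherapy would be unsuitable. Group B and C patients had therefore been accepted as suitable for a single drug. What is at stake is the safety of a small and unknown number of patients, and to a lesser extent the regimen they take for the rest of follow-up.

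**Working it through.** No power, alpha or rate enters this point, and the plan states no figure to reproduce. The check sets the provisions side by side.

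**Step 1: who is routed to the rules.** Section 18.2, item 3, covers GI bleeding after randomization in any group, with unblinding permitted. The post-randomization pathway in 18.1 covers any group, with unblinding required.

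**Step 2: what can be restarted.** Section 5.5.2 bars study drug after unblinding, so anything restarted is open-label.

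**Step 3: active antiplatelet drugs before the bleed (5.6.2) and after the literal rule (18.3).**

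| Group | Before the bleed | Branch 1, by day 5 after hemostasis | Branch 2, day 7 after hemostasis |
|---|---|---|---|
| A | 2 | 2 | 2 |
| B | 1 (aspirin) | 2 | 2 |
| C | 1 (clopidogrel) | 2 | 2 |

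Both branches, 2 of 2, end in two drugs. For groups B and C that is one more than before.

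**Step 4: can *resume* be read as the patient's own regimen?** Not in branch 1. For group B, the drug to be given first is clopidogrel, which had been placebo since randomization. For group C, the aspirin to be resumed had been placebo.

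**Step 5: does other text settle which instruction governs?** Three protocol provisions give discretion or local standard of care: 5.5.2, 5.9.2 and the last sentence of 18.2, item 3. Only the last is linked to the rules, and it gives a loose sequence: apply the rules, then discretion is allowed once the bleeding is cured. Cure is not defined. Branch 1 itself starts only when the injury is controlled, and both restart days count from hemostasis, so the restart period and the period of discretion overlap. Sections 5.5.2 and 5.9.2 are not ranked against Appendix 4.

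**Step 6: effect on the endpoints.** All bleeding and NACE are time-to-event analyses (SAP 9.3.2), so an overt triggering bleed has usually counted already. A bleed-driven endoscopy that shows a new lesion already counts for the primary endpoint (11.1). What remains is later TLF or stent thrombosis in a group B or C patient then taking two drugs, counted in the assigned group.

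**The case against.** The best reply is that the discretion clauses already fill the gap. The case concerns an unblinded patient, so the physician knows that only one drug was being taken, can see that a rule about stopping and resuming DAPT does not fit, and can turn to 5.5.2, 5.9.2 or the end of 18.2, item 3. Much of this stands: the step-up is avoidable and a careful physician would probably avoid it. But 18.2, item 3, also tells that physician to adjust antiplatelet therapy by the rules, and those rules name both drugs and the days.

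Several stronger readings are tempting, and the documents do not support them:

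- *That the protocol gives no order at all.* Section 18.2, item 3, does give one. It is incomplete.
- *That groups B and C have no branch anywhere.* A figure inside 18.3 is not shown, so this can be said only of the visible prose.
- *That two drugs are restarted within a week of the bleed.* Days 5 and 7 run from hemostasis, and the interval from onset may be longer.
- *That a still-blinded bleeder is also covered.* No claim is made either way. Section 5.9.1, on resuming blinded tablets, is written for events such as surgery, with a limit under 7 days, and is a weak guide here.
- *That occult bleeders with no lesion are covered.* The title of 18.3 is "The treatment principle of clinically-driven or AMCE-positive gastrointestinal (GI) bleeding", and its restart clock needs gastroscopic hemostasis.

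**Conclusion.** The point holds as a minor patient-safety inconsistency in the current protocol. On the visible text, the rules to which unblinded post-randomization bleeders are sent would take group B and C patients from one active drug to two. The provisions that would prevent this are not clearly given priority. The conclusion assumes that the figure in 18.3 does not branch by group.

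Its size in patients cannot be stated, because the documents give no post-randomization bleeding rate. A reader might infer a material bias in the trial's results; the documents do not support that. The primary analysis, power and analysis sets are untouched, and the triggering event has in most cases already been counted.

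**What to change.** In 18.3 and at the head of Appendix 4, limit the steps that stop and then resume DAPT to patients known to be on DAPT: those who bleed before randomization, and group A patients after unblinding. State that for unblinded group B and C patients, antiplatelet therapy after a bleed follows physician discretion and local standard of care, with no default two-drug restart.

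Two clerical pointers in 18.2, item 3, can be corrected at the same time. The reference to Appendices 1 to 3 leads to definitions and scores and should point to 18.3. The reference to Part 5.4 leads to incorrectly enrolled subjects and should point to 5.5.2.

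The cost is a wording amendment, with the ethics approval that 8.2 requires, and a letter to sites. No patients, procedures or data collection are added.
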